#### Health Care Professionals

Telephone interviews will also be held with medical staff from both primary and secondary care who worked at the clinics. The anticipated number of participants will be 10 from primary care and 10 from secondary care. All staff who attended the MISSION clinics will be approached for consent. The interviews will explore the health care professionals’ thoughts on MISSION and its strengths and weaknesses as well as any suggestions for improvement. The interviews will also explore the health care professionals’ understanding and training in severe asthma and any areas where they would wish to see improvement.

#### Interview Structure

The semistructured interviews will be conducted by telephone and audio-recorded with notes taken. Telephone interviews have been chosen as participants live over a wide geographical area, and it will allow flexibility with interview times to accommodate participants’ work and other commitments.

The interviews will be conducted by one of the health care professionals involved in the clinic. By having an existing relationship with the study participants and by the interviewer being a health care professional, the participant may be more willing to share experiences and personal views [7,8]. The researcher will be aware of the potential conflict with the professional role and the role as interviewer and will ensure open questions are asked [9]. The skills required during a clinical consultation have considerable overlap with the skills in qualitative interview [7,9]. It is important that the relationship between the interviewer and interviewee is clear when planning the qualitative interview [10] as it is recognized that this can be a factor in the interview.

At the beginning of the interview, patient participants will be reminded that the interview topic guide can be deviated, that they are free to suggest topic areas relevant to their experience and tell their experiences in their own words, and that there are no right or wrong answers but to share with the interviewer their thoughts, both the positives and negatives about MISSION, living with asthma, and asthma care.

There is also a concern that the patient participants may raise health questions or ask for health care advice. This will be addressed by explaining at the beginning of the interview that the interview is not a clinical consultation; however, any questions can be answered at the end of the interview.

#### Interview Analysis

The interviews will be digitally audio-recorded and transcribed by a professional transcription company. The data will be entered into a software program to facilitate qualitative analysis (NVivo10, QSR International (UK) Ltd, London, UK). All participants’ names will be removed from the transcripts to retain confidentiality. When writing the results, no quotes will be directly attributed to participants. Participants will be given the opportunity to read and approve the transcript. The transcript will be sent to participants, and if no response is heard within 2 weeks, the transcript will be included in the analysis.

The results from the interview will be analyzed using a thematic and framework analysis, which uses a 5-step approach to analyzing and writing up data [11]. This involves familiarization with the interviews, identifying themes, indexing the themes onto the interview transcripts, charting, and mapping the themes. The themes from the patient and health professionals’ interviews can be compared. This will enable key themes to be systematically identified and to map the themes from the patients against those from the health care professionals. A random sample of 5 interviews will also be independently assessed by the supervisor to review the themes and analysis undertaken.

The interviews will take between 45 min to 1 hour to complete depending on what the participants share with the interviewer. The interview can be terminated at any point the participant wishes to stop, and this will not influence their subsequent treatment.

### Sample Size

The study was powered to show a difference between the MISSION group and the primary care group for the primary outcome, exacerbation frequency. The sample size was based on an analysis of covariance (ANCOVA) approach, with the outcome being exacerbation frequency in the second 6-month period and with the exacerbation frequency in the first 6-month period being the covariate. Baseline data suggest a mean number of exacerbations for this group of 1.29, with an SD of 1.30. There is expected to be no change in exacerbation frequency between time periods for the primary care group, whereas it is anticipated that exacerbations in the MISSION group may reduce by 50% to 0.65 exacerbations. A correlation between the exacerbation rates in the 2 time periods of 0.5 is assumed. The primary care group will be larger, with an anticipated 3:1 ratio. To show a difference between groups with a 5% significance level and 90% power, it is calculated that 44 subjects in the MISSION group and 132 in the primary group are required.

### Data Analysis

#### Description of Analysis Populations

All data collected will be analyzed. There will be an analysis of the MISSION and outpatient groups separately. We will analyze 4 groups of participants: (1) qualitative assessments in participants attending the severe clinic, (2) health professionals attending either of the rapid or severe clinics, (3) quantitative assessments between those attending the rapid clinic in primary care to those invited but did not attend, and (4) those who attended the severe clinic compared with those routinely attending the outpatient severe asthma clinics in hospital.

#### Analysis of Endpoints

The analyses will compare the study outcomes between the 4 study groups.

The primary outcome is exacerbation frequency. This outcome will be analyzed using ANCOVA, with the outcome variable being exacerbation frequency in the second 6-month period and the exacerbation rate in the first 6-month period treated as the covariate. Owing to the likely skewed distribution of the exacerbation frequency, it may be necessary to perform a log transformation of the outcome before analysis. Comparisons will be made overall between the 3 groups, and specifically between the MISSION group and each of the other 2 groups.

The analysis of secondary outcomes measured on a categorical scale during the second 6-month period will be compared between groups using Fisher exact test. Continuous variables will be compared between groups using analysis of variance, if found to be normally distributed, or the Kruskal-Wallis test, if not found to be normal.

Comparisons between groups will also be made accounting for the values during the first time period. ANCOVA will be used for continuous variables, whereas logistic regression will be used for binary outcomes.

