#### Modern Innovative Solutions to Improve Outcomes in Rapid Access Asthma Clinics

Lung function including FEV1, FVC, peak flow, and FeNO.ACQ and AQLQ at baseline, 3 months, and 6 months in MISSION RAAC patients.Medication history for the last 12 months.Exacerbation history for the last 12 months.OOH, hospital, and emergency department attendances

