## Results

### Quantitative

The MISSION team screened GP records to identify uncontrolled asthmatics to invite to MISSION clinics. There were 369 patients identified who had one or more of the criteria that suggest uncontrolled or potentially severe asthma (high inhaled corticosteroid dose >500 mcg BDP (Beclomethasone Diproprionate) , 2 or more exacerbations in the last 12 months requiring steroids for more than 3 days, any hospital, ED or OOH contact in the last 12 months, and high SABA usage—>6 inhalers in the last 12 months or reduced lung function FEV1 ≤70%). All patients who were identified were approached for the MISSION project.

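### The primary ANCOVA adjusts a self-selected comparison for one 6-month exacerbation count only; the preceding 6 months could be added as a second covariate for the RAAC versus primary care contrast, for a gain that ranges from nil to modest

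*Protocol article*

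**What the plan says.** Under Analysis of Endpoints, the primary outcome is exacerbation frequency in the second 6-month period, analysed by ANCOVA with "the exacerbation rate in the first 6-month period treated as the covariate". No other covariate is named. Sample Size rests on the same model and adds: "A correlation between the exacerbation rates in the 2 time periods of 0.5 is assumed".

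The groups are not randomised. Description of Analysis Populations compares RAAC attenders with people who were invited but did not come.

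Three other places bear on how much history is available:

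- Results, Quantitative, lists the record-screening criteria. One of them is "2 or more exacerbations in the last 12 months requiring steroids for more than 3 days". Meeting any one criterion was enough.
- The Results section on RAAC and SAAC patients says that 1436 patients found by the searches were manually reviewed. Non-attenders came from the same GP search (Results, Primary Care Patients).
- The RAAC part of Quantitative Data Collection lists "Exacerbation history for the last 12 months". For the RAAC versus primary care comparison, the secondary outcome list gives 6-month windows only.

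**The concern.** A count over 6 months is a noisy measure of a patient's underlying exacerbation rate. When groups form by self-selection, ANCOVA removes only the part of a true baseline difference that the covariate captures, and the rest is read as treatment effect. The pre-clinic count is the only named protection in the powered comparison, so its weakness matters. The bias could go either way: if attenders exacerbate persistently more than non-attenders, the benefit is understated; if less, it is overstated. Screening already looked at a further 6 months of the same records, and the model does not use them.

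**Working it through.** **Inputs (Sample Size).** "Baseline data suggest a mean number of exacerbations for this group of 1.29, with an SD of 1.30". Effect: "exacerbations in the MISSION group may reduce by 50% to 0.65 exacerbations", so delta = 1.29 - 0.65 = 0.64. Control group: "There is expected to be no change in exacerbation frequency between time periods for the primary care group". Target: "To show a difference between groups with a 5% significance level and 90% power", taken as two-sided because sidedness is not stated. Correlation r = 0.5; ratio 3:1; stated size 44 and 132. All figures are on the untransformed scale, as in the plan's own calculation.

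**1. Reproduce the plan's figure.** Residual SD = 1.30 × √(1 - 0.5²) = 1.126. MISSION n = (4/3) × [1.126 × (1.960 + 1.282)/0.64]² = 43.35, rounded up to 44, with 132 controls. SE = 1.126 × √(1/44 + 1/132) = 0.196. Power = Φ(0.64/0.196 - 1.96) = 90.4%. The sample size reproduces.

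**2. What one 6-month covariate leaves.** With equal SDs the ANCOVA slope equals r. A difference D present in both periods therefore leaves D - rD = (1 - r)D, which is half of D at r = 0.5.

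**3. Add months -12 to -7 as a second covariate.** Let adjacent periods correlate at r1 and periods two apart at r2. The coefficients are:

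- recent count: b1 = (r1 - r1·r2)/(1 - r1²)
- earlier count: b2 = (r2 - r1²)/(1 - r1²)

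The share left is 1 - b1 - b2, and the residual variance factor is 1 - (r1·b1 + r2·b2). The article gives r1 = 0.5 and does not give r2, so r2 is an assumption and is shown as a range.

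| r1 | r2 | b1, b2 | Share left: one → two covariates | Variance factor: one → two |
|---|---|---|---|---|
| 0.5 | 0.5 | 0.333, 0.333 | 50% → 33% | 0.750 → 0.667 |
| 0.5 | 0.4 | 0.400, 0.200 | 50% → 40% | 0.750 → 0.720 |
| 0.5 | 0.25 | 0.500, 0 | 50% → 50% | 0.750 → 0.750 |
| 0.3 | 0.3 | 0.231, 0.231 | 70% → 54% | 0.910 → 0.862 |
| 0.7 | 0.7 | 0.412, 0.412 | 30% → 18% | 0.510 → 0.424 |
| 0.237 | 0.237 | 0.192, 0.192 | 76% → 62% | 0.944 → 0.909 |

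The last row comes from the plan's own mean and SD. If each patient has a stable rate and counts are Poisson around it, the implied correlation is (1.30² - 1.29)/1.30² = (1.69 - 1.29)/1.69 = 0.237.

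**4. Power at 44/132.** Power = Φ(0.64/[1.30 × √(variance factor) × √(1/44 + 1/132)] - 1.96).

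- Equal correlations of 0.5: 90.4% → 93.4%. The n for 90% power would fall from 44/132 to 39/117.
- Equal correlations of 0.237: 82.9% → 84.3%.
- 0.5 decaying to 0.25: stays at 90.4%.

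**5. Size in exacerbations.** Take a persistent difference of 0.30, which is illustrative and not from the article. At equal correlations of 0.5 the bias is 0.15 with one covariate and 0.10 with two. A simulation of 10,000 runs at 44/132, using the sum of the two baseline counts (equivalent here, since b1 = b2), gave 0.151 and 0.100. The improvement of 0.05 is about 8% of the target (0.05/0.64).

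**6. Why separate covariates.** A single 12-month total has variance factor 1 - (r1 + r2)²/(2 + 2·r1). With decay to 0.25 this is 1 - 0.75²/3 = 0.812, worse than the 0.750 of the present model; power falls to 88.1% and the MISSION n rises to 47. Two separate terms avoid that loss.

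**The case against.** The strongest reply is that nothing in the article is misstated. A 6-month baseline paired with a 6-month outcome is used consistently, the sample size follows from it, and a second baseline term is a refinement. That is fair as far as it goes; the point concerns the strength of the only named adjustment.

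Other parts of the reply also stand:

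- **The gain needs a correlation the article does not give.** Only one between-period correlation is stated, and the honest range of benefit includes zero. Selection partly on 12-month history may also alter these correlations in the sample.
- **No 12-month count is shown to be on file.** A reader might infer from the screening criterion that it is. The criterion is a threshold among alternatives, so a patient could qualify on inhaled steroid dose alone. It asks for steroids beyond 3 days with no dose, whereas Primary Outcome Measure for All Patients requires at least 30 mg prednisolone or equivalent for at least 3 days. The 12-month history in the RAAC list does not settle it: it sits under the RAAC heading only and, as notes are reviewed 6 months after the clinics, may mean 6 months before plus 6 after.
- **The hospital outpatient group did not pass through this screen.** Analysis of Endpoints compares three groups, and the article lists only 6 months of pre-clinic data for outpatients.
- **Season is not a demonstrated bias.** With clinics in June and July, the baseline and outcome windows fall in different seasons, and a reader might infer bias from that. Attenders and non-attenders came from the same search, however, and a seasonal shift common to both cancels in the contrast.
- **Precision is not the pressing need.** 84 patients attended the RAACs against 44 required, subject to consent.

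What the reply does not remove is that the planned adjustment leaves half of a persistent difference on the plan's own assumption, that the records reach back far enough to do better, and that a second separate term costs almost nothing if it proves uninformative.

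**Conclusion.** The point holds in limited form. At the plan's correlation of 0.5, with equal SDs and a difference that persists over time, the single 6-month covariate leaves half of that difference in the attender versus non-attender estimate.

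A reader might infer that choosing 6 rather than 12 months causes the whole of this, or that 12 months would cure it. Neither follows. Even with equal correlations of 0.5 a third remains, so the choice of window accounts for one sixth of the difference (1/2 - 1/3). Nor does the half apply to every baseline difference or every correlation: the share left by the present model is 30% at 0.7 and 76% at 0.237. The precision gain is at most modest at 0.5 (about 11% of residual variance, 3 points of power) and nil under decay to 0.25. The stated 44/132 is not in error.

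The change is worth making because it strengthens the only named bias control at small cost, but self-selection remains the main limitation.

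**What to change.** In Analysis of Endpoints, for the RAAC versus primary care contrast:

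1. Count exacerbations in months -12 to -7 in both groups, using the primary outcome definition rather than the screening criterion.
2. Enter that count as a second covariate beside the count for the most recent 6 months. Do not combine the two into one 12-month total.
3. Keep the 6-month outcome and the 44/132 sample size.
4. State that residual confounding remains after adjustment.
5. Leave the hospital outpatient contrast on the 6-month covariate unless the same earlier counts can be obtained for that group.

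The cost is 6 more months of extraction within a notes review already planned, and one degree of freedom. The study team should confirm that the extraction fits the article's commitment to use existing records only. If the earlier counts cannot be extracted on the same definition in both groups, keep the present model and report the limitation.

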### Primary and Secondary Endpoints and Outcome Measures for Quantitative Study

#### Primary Outcome Measure for All Patients

The primary endpoint is asthma control as measured by exacerbation frequency (defined as deterioration in symptoms requiring ≥30 mg prednisolone or equivalent for ≥3 days).

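### The log transformation held in reserve for the primary exacerbation count is undefined for the many patients expected to have none, and every workaround distorts the estimate

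*Protocol article*

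**What the plan says.** The Primary Outcome Measure section states: "The primary endpoint is asthma control as measured by exacerbation frequency". An exacerbation there is a steroid-treated episode, so the outcome is a small whole number that can be zero.

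Under Analysis of Endpoints: "This outcome will be analyzed using ANCOVA, with the outcome variable being exacerbation frequency in the second 6-month period", with the first-period rate as covariate. The same paragraph expects the outcome to be skewed and says "it may be necessary to perform a log transformation of the outcome before analysis". It gives no added constant, no rule for zeros, no criterion for choosing between scales, and no count model.

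The Sample Size section works on the untransformed count: "Baseline data suggest a mean number of exacerbations for this group of 1.29, with an SD of 1.30". Primary care patients are assumed to stay at that level, while for the intervention "it is anticipated that exacerbations in the MISSION group may reduce by 50% to 0.65 exacerbations". The two periods are taken to correlate at 0.5. The section arrives at 44 MISSION and 132 primary care patients.

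The section on missing, unused and spurious data says that everything collected goes into the analysis. No section states what share of patients is expected to have no exacerbation.

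**The concern.** A log transformation suits a positive, right-skewed measurement. Here the skew comes from a small count with many zeros, and zero is the result the service hopes to produce. If the fallback is used as written, it cannot be computed for a large share of patients, and for more of them in the MISSION group than among controls.

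The analyst would then have to improvise. Leaving out the zeros conditions the comparison on having had an exacerbation after the intervention and pulls the estimate towards no effect. Adding a constant keeps everyone, but gives an estimate that is neither a difference in mean counts nor a rate ratio, and its size is set by the constant. Both the scale and the constant would be chosen with the data in view, for the primary outcome.

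**Working it through.** **1. The plan's own figure.** Inputs from Sample Size: means 1.29 and 0.65 (difference 0.64), SD 1.30, correlation 0.5, 5% significance (taken as two-sided), 90% power, 3:1 ratio.

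- Residual SD after adjustment: 1.30 × √(1 − 0.5²) = 1.126.
- MISSION n = (1 + 1/3) × [1.126 × (1.960 + 1.282) / 0.64]² ≈ 43.4, so 44. Controls = 3 × 43.4 ≈ 130, and 3 × 44 = 132.
- The noncentral t version gives exactly 44 and 132, with power 0.901.

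The stated size reproduces, on the untransformed scale.

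**2. Expected share of zeros.** The variance is 1.30² = 1.69. A negative binomial with that mean and variance has k = 1.29² / (1.69 − 1.29) = 4.16, and P(0) = (k / (k + mean))^k. Poisson gives P(0) = e^(−mean).

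| Assumption | Primary care, mean 1.29 | MISSION, mean 0.65 |
|---|---|---|
| Poisson | 27.5% | 52.2% |
| Negative binomial, k = 4.16 | 32.5% | 54.7% |
| Negative binomial, SD held at 1.30 | 32.5% | 67.8% |

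One bound needs no distribution. A whole-number count with mean 0.65 can be 1 or more in at most 65% of patients, so at least 35% must be zero. No such bound exists at a mean of 1.29.

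**3. Consequence of each way of taking logs.** Correlated negative binomial counts (k = 4.16) were simulated with the planned means and a between-period correlation of about 0.5, in groups of 44 and 132. The true ratio is 0.65 / 1.29 = 0.50. Ratios come from large-sample runs, except for the count model, whose ratio is the average over simulated trials. Power comes from 2,000 to 4,000 simulated trials; ranges show two separate simulations.

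| Analysis | Estimated ratio | Power |
|---|---|---|
| Untransformed ANCOVA | (recovers the difference of 0.64) | 97% |
| log(y), zeros dropped | 0.76-0.77 | 64-66% |
| log(y + 0.01) | 0.29 | 88-90% |
| log(y + 0.1) | 0.48 | 92% |
| log(y + 0.5) | 0.66 | 95-96% |
| log(y + 1) | 0.75 | 96-97% |
| Poisson regression, robust SE, first-period count as covariate | 0.49 | 97% |

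With zeros dropped, about 20 of 44 MISSION and 89 of 132 primary care patients remain, and a 50% reduction is reported as roughly 23-24%. With a constant, the reported reduction runs from 25% to 71% on the same data. The result at 0.1 lies near the truth only by coincidence.

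**The case against.** The strongest reply is that the article plans ANCOVA and mentions the log only as a possibility. That stands. A reader might infer that the planned primary analysis is underpowered or that ANCOVA itself is invalid here. The documents do not support this: untransformed ANCOVA has about 97% power in the simulation, and the 44 and 132 are correct for it.

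Second, nothing in the article says that zeros will be dropped, and doing so would go against its statement that all collected data are analysed. That also stands. The loss of power is therefore what one way of carrying out the fallback would cost, not something the plan commits to. A reader might also arrive at a power below 50% for that variant. A model with a single shared gamma effect and k = 4.16 gives 46-48%, but its between-period correlation among primary care patients is only about 0.40 / 1.69 = 0.24, where 0.40 is 1.29² / 4.16. At the protocol's 0.5 the figure is about 65%.

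Third, log(y + 1) keeps its power, and a condensed article may leave the constant to the full analysis plan. This stands in part. Naming a constant would make the transformation computable and settle which one is used. It would not stop the estimate from depending on it. The point concerns the method that the article names, not a missing detail.

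**Conclusion.** The point holds for the fallback, not for the untransformed ANCOVA. On the plan's own means and SD, a plain log of the outcome is undefined for about 28-33% of primary care patients and about 52-55% or more of MISSION patients. Dropping them would contradict the article, shrink a true ratio of 0.50 to about 0.77 and leave about 65% power. Adding a constant leaves power largely intact but lets the ratio range from 0.29 to 0.75 according to the constant. The choice of scale is left open until the data are seen.

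The zero shares are implied by an assumed count distribution, not quoted in the article; only the minimum of 35% in the MISSION group is free of that assumption. The bias and power figures rest on negative binomial counts with k = 4.16 and a correlation near 0.5. The sample size is not in error.

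**What to change.** In Analysis of Endpoints, delete the log-transformation option. Prespecify a negative binomial regression of the second-period count (or Poisson with robust standard errors), with a log link and the first-period count as covariate, and report a rate ratio with its 95% confidence interval. Untransformed ANCOVA with robust standard errors can stay as a supportive analysis, which keeps the link to the sample-size calculation.

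This takes one paragraph of wording, no new data and no extra patients. At the planned size the count model has about 94-97% power across the settings checked with k = 4.16, and roughly 87-91% if patients are more heterogeneous (k between 1 and 2). An observed-time offset, and count models for the secondary counts, are optional and not needed to correct this point.

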#### Primary Objectives

The primary objectives of this study are as follows:

To assess whether asthma control (assessed by exacerbation history, Asthma Control Questionnaire (ACQ), health care utilization, and short-acting beta-agonist (SABA) usage) is improved in MISSION SAAC patients compared with patients undergoing standard outpatient secondary asthma care at 6 months.To assess whether asthma control (assessed by exacerbation history, health care utilization, and SABA usage) is improved in MISSION RAAC patients compared with those who were eligible for MISSION but did not attend.To assess whether asthma control (assessed by exacerbation history, health care utilization, and SABA usage) is improved after attending the MISSION RAAC and SAAC.

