### Modern Innovative Solutions to Improve Outcomes in Rapid Access Asthma Clinic Patients and Severe Asthma Assessment Clinic Patients

The MISSION service: The searches identified 1436 patients who were manually reviewed by the MISSION team and 460 patients met the criteria. All these patients were invited to the clinic; 125 were booked in, and 84 attended the RAACs, of whom 22 were identified for the SAACs.

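### The primary ANCOVA sets one undefined MISSION group against both controls, which does not match the two separate contrasts in the objectives and analysis populations

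*Protocol article*

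**What the plan says.** Analysis of Endpoints opens with this sentence: "The analyses will compare the study outcomes between the 4 study groups". For exacerbation frequency it continues: "This outcome will be analyzed using ANCOVA, with the outcome variable being exacerbation frequency in the second 6-month period", with the rate in the first 6 months as covariate. It then fixes the comparisons: "Comparisons will be made overall between the 3 groups, and specifically between the MISSION group and each of the other 2 groups".

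The Primary Objectives are organised differently. Objective 1 asks whether control "is improved in MISSION SAAC patients compared with patients undergoing standard outpatient secondary asthma care at 6 months". Objective 2 asks whether it "is improved in MISSION RAAC patients compared with those who were eligible for MISSION but did not attend". Objective 3 is a before-after question.

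The Description of Analysis Populations repeats the two between-group pairings. Its third item is "quantitative assessments between those attending the rapid clinic in primary care to those invited but did not attend" and its fourth is "those who attended the severe clinic compared with those routinely attending the outpatient severe asthma clinics in hospital". Its first two items are the interviewed severe-clinic patients and the health professionals.

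On numbers, the Results state that "84 attended the RAACs, of whom 22 were identified for the SAACs". The outpatient sample is set at 20, to equal the number attending the SAACs. The Sample Size section powers only MISSION against primary care, with 44 and 132 subjects.

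**The concern.** The article states its primary comparisons in two ways that cannot both be followed. The objectives and populations pair each clinic with its own control. The analysis section takes one MISSION group and compares it with both controls, after an overall test across three groups.

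What is at stake is mainly the outpatient contrast. Patients went on to the SAAC because the RAAC team judged their asthma potentially severe and uncontrolled. Outpatient controls are new referrals to a severe asthma clinic. If the MISSION side of that contrast is every RAAC attender, a difference in exacerbations could reflect who is in each group as well as which service they received. If RAAC-only patients exacerbate less than specialist referrals, the error favours MISSION.

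The overall 3-group test combines primary care non-attenders and hospital referrals as controls, and no objective asks for that. The announced 4-group comparison also has no clear meaning for an exacerbation outcome.

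**Working it through.** **1. The plan's own sample size.** Inputs from Sample Size: mean 1.29, SD 1.30, reduction to 0.65 (difference 1.29 − 0.65 = 0.64), correlation 0.5, ratio 3:1, 5% significance (taken as two-sided), 90% power.

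- Residual SD = 1.30 × √(1 − 0.5²) = 1.126.
- MISSION n = (1 + 1/3) × [1.126 × (1.960 + 1.282) / 0.64]² = 43.35, rounded up to 44; primary care 3 × 44 = 132.

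This matches the stated 44 and 132 (power 90.4%). The calculation is not in dispute, but it covers one contrast only.

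**2. Can any definition of the MISSION group serve both contrasts?**

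| Reading of the MISSION group | Against non-attenders | Against outpatients |
|---|---|---|
| All RAAC attenders (84) | Fits objective 2 | Does not fit objective 1 |
| RAAC plus SAAC | Same 84 people, because SAAC patients came from the RAAC | Does not fit objective 1 |
| SAAC only (20–22) | Does not fit objective 2; cannot supply 44 subjects | Fits objective 1 |

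None does. The first two readings are the natural ones, since only they can supply the 44.

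**3. The 4-group sentence.** Taken from the populations list, the four include interviewees and staff, and the other two items are already contrasts. Taken as the four patient categories in the eligibility criteria, RAAC and SAAC overlap, so they are not independent groups. Neither reading gives a valid 4-group comparison.

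**4. Mix of the MISSION side on the natural reading.** 84 − 22 = 62, and 62/84 = 74% were not identified for the SAAC. If the 20 attenders are counted instead of the 22 identified, it is 64/84 = 76%.

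**5. What baseline adjustment removes.** With equal SDs in the two periods, the ANCOVA slope is about the correlation, 0.5. If two groups differ by a stable amount g in both periods with no service effect, the adjusted difference is g − 0.5g = 0.5g, so half remains.

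The article gives no exacerbation rate for outpatient referrals, so the size is unknown. As an illustration only, assume SAAC patients have the outpatients' rate and RAAC-only patients run G exacerbations per 6 months below it. Then the remainder is 0.738 × G × 0.5:

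| Assumed G | Remaining difference |
|---|---|
| 0 | 0 |
| 0.25 | 0.09 |
| 0.5 | 0.18 |
| 1.0 | 0.37 |

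**6. Power of SAAC against outpatients.** The article gives no inputs for this contrast. Assume those in step 1 apply, with 20 per arm.

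- Standard error = 1.126 × √(1/20 + 1/20) = 0.356.
- 0.64 / 0.356 = 1.80.
- Power is about 42% with the t distribution and 44% with the normal approximation (43% and 45% at 22 against 20).
- On the normal approximation, 90% power would need 66 per arm and 80% would need 49.

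**The case against.** The strongest reply is that the sentence is loose shorthand in a condensed article. It never says that RAAC and SAAC patients are merged for the outpatient contrast. The section just before it gives the correct pairings, the secondary outcome lists and Table 1 follow them, and the outpatient sample is sized to SAAC attendance. A careful analyst might therefore run the right contrasts. This stands in part: pooling is an inference from an undefined term, and the article does not state it. But Analysis of Endpoints is the section that prescribes the primary model, and the shorthand has no reading that fits both pairings.

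Three stronger readings are tempting and should be resisted.

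- **That the 62 are non-severe, or did not need the severe clinic.** Every invitee met criteria suggesting uncontrolled or potentially severe asthma. The article says only that these patients were not identified for the SAAC.
- **That objective 1 is left without any analysis.** The SAAC and outpatient populations are named as a comparison, exacerbation frequency before and after is listed among their secondary outcomes, and the section's general provisions allow baseline-adjusted comparisons. What is missing is a primary model that matches the objective.
- **That the bias has a known size.** It depends on an outpatient rate that the article does not give, and it could be nil.

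It is also fair to say that the powered contrast is unaffected. The article openly limits its power statement to MISSION against primary care and describes the study as an evaluation ahead of a larger randomized trial.

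**Conclusion.** The concern holds as an internal contradiction. The primary analysis names one undefined MISSION group for two contrasts that the objectives and populations keep apart, and it adds an overall test that serves no objective. This rests on the text and on the subset relation between the clinics, and needs no assumed figure.

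Followed on its natural reading, the outpatient contrast would put about 84 patients (or those who consent), 74% of them not identified as potentially severe and uncontrolled, against specialist referrals. Baseline adjustment would leave about half of any stable gap, given a correlation of 0.5 and equal SDs. The direction and size of that gap are not documented.

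The figure of 42–44% power for SAAC against outpatients holds only if the Sample Size inputs carry over to a population for which they were not stated. RAAC against non-attenders is the same comparison on the natural reading, and its 44 and 132 stand.

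**What to change.** In Analysis of Endpoints, replace the 3-group comparison with two ANCOVAs of exacerbation frequency in the second 6 months, each with the first-period rate as covariate:

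- (a) all RAAC attenders, including those sent on to the SAAC, against invited non-attenders;
- (b) SAAC attenders against outpatient new referrals.

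Delete the overall 3-group test and the 4-group sentence. State that the sample size covers only (a). Report (b) as an estimate with a 95% confidence interval; if a power figure is given, say that it borrows the inputs of (a). Objective 3 keeps its own before-after analysis.

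The change is one of wording. It needs no new data and leaves the sample size as it is. Objective 1 can remain a primary objective; whether to rank the objectives is a separate design choice for the investigators. The cost is that the limited precision of (b) becomes explicit.
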